### **Primary Objective**

To test the efficacy of three financial incentive structures in combination with technology intensified diabetes education and skills training intervention on HbA1c levels in AAs with T2DM.

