### **Data Collection Strategy**

**Personnel:** Two half-time masters-level trained diabetes educators (DEs) will deliver the interventions; one full-time research assistant (RA) will conduct screening, consent, enrollment procedures, and questionnaire administration; a half-time data entry clerk (DC) will be responsible for data entry; and a part-time masters-level statistician will be responsible for data management (DM). Each potentially eligible patient will be asked to report for a screening visit. At this visit, the following will be collected: basic demographic information, screening information, and a blood sample for a screening hemoglobin A1c (HbA1c) value. Basic demographic information will be collected to compare those screened to those randomized. Individuals who have a screening HbA1c of  $\geq 8$  will be asked to return within two weeks for a baseline visit. At the baseline visit, a full battery of questionnaires will be administered, and individuals will be randomized. All individuals randomized will have follow-up visits at 3 months, where survey questionnaires will be administered, and blood collected for HbA1c. Blood pressure will also be measured at the baseline and 3 months follow-up visit.

**Primary Outcome Measure: HbA1c:** About 10cc of blood will be drawn by trained phlebotomists and sent to the lab for HbA1c.

**Secondary Outcome Measures: Blood Pressure:** Blood pressure readings will be obtained using automated BP monitors (OMRON IntelliSense™ HEM-907XL). The device will be programmed to take 3 readings at 2 minute intervals, and give an average of the 3 BP readings. **Resource Utilization & Cost:** Previously validated questions on resource utilization will be administered. The questionnaires are 1 page long and capture information on hospitalizations, physician/professional visits, and medications. **Quality of Life:** The SF-12 (Ware 1996) is a valid and reliable instrument to measure functional status. The SF-12 items reproduce at least 90% of the variance in PCS-36 and MCS-36 scores.

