**Sample Size and Power.** For the primary/secondary efficacy outcomes, HbA1c (Primary) and BP/QOL (Secondary), with 18 subjects randomized to each of the three intervention groups, we will have 85% power to detect at least a 1.0 standardized effect size (difference in within group means in sd units). This calculation assumes that the primary/secondary efficacy outcomes are measured at 2 time points (baseline and 3-months); the intra-class correlation for repeated observations is no greater than 0.5; level of significance ( $\alpha$ ) =0.05, two-tailed test. Assuming that HbA1c measurements have a standard deviation of approximately 1.5 based on our pilot studies, the study has 85% power to detect a difference of 1.0 percentage points (raw units) change in HbA1c within each of the three comparisons groups. Analyses for continuous secondary/exploratory outcomes (behavioral and process variables) also have 85% power to detect a standardized effect size of 1.0sd. To account for the "fraction of missing" information that must be imputed in the ITT sample and the dilution effect of ITT analyses (Hsieh et al., 2003) the sample size is inflated by 10% to achieve a final ITT sample size of 20 subjects randomized to each treatment group (N=60).

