## Data Analysis

### Design/Analysis Issues

Analysis sets. The intent-to-treat (ITT) sample, comprising all randomized patients, will be used for the primary analyses. The per protocol/completer sample will comprise subjects who were compliant with protocol requirements and for whom all required measurements over 3-months of follow-up have been made. Analyses will be carried out separately for ITT and per protocol samples to test sensitivity of conclusions to drop-outs/nonadherence. If differences are present between the per protocol and ITT analysis sets, the characteristics of the two analysis populations will be examined to aid in explaining any discrepancies.

**Analysis Plan for Primary Aim (Efficacy):** To test the efficacy of three financial incentive structures in combination with technology intensified diabetes education and skills training intervention on HbA1c levels in AAs with T2DM. Preliminary analyses will be conducted to assess the similarity of the treatment arms based on collected variables. Univariate descriptive statistics and frequency distributions will be calculated, as appropriate for all variables along with two-sided 95% confidence intervals when appropriate. Study discontinuation (attrition) rates will be estimated for each group. The preliminary analyses will describe the pre-specified covariates as well as identify potential confounding (prognostic) variables to be used as covariates in subsequent secondary analyses. Covariates to be examined in the preliminary analyses and potentially used in secondary analyses include age, sex, income, health literacy, social support, depression, and comorbidity. The primary framework for analysis is paired t-test. Change in HbA1c from baseline to 3-months (dependent variable) will be examined in each treatment arm (high, moderate and low frequency of financial incentives) using a type I error rate of 0.05.

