### Analysis Plan for Secondary Aims:

1. To test the efficacy of three financial incentive structures in combination with technology intensified diabetes education and skills training intervention on blood pressure and quality of life in AAs with T2DM.

2. To test the efficacy of three financial incentive structures in combination with technology intensified diabetes education and skills training intervention on diabetes knowledge and self-care behaviors (medication adherence, diet, exercise).

Similar to the primary analysis, paired t-test will be used to evaluate change in BP, QOL, knowledge and self-care variables from baseline to 3-months (dependent variables) within each treatment arm (high, moderate and low frequency of financial incentives) using a type I error rate of 0.05.

**Analysis Plan for Exploratory Analyses.** Exploratory analyses to examine frequency of session attendance, frequency of uploads and average weekly glucose within the three different financial incentive structures. Univariate descriptive statistics and frequency distributions will be calculated, as appropriate for all variables along with two-sided 95% confidence intervals when appropriate.

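### Every specified primary and secondary test compares an arm with its own baseline; no between-arm test or estimate is given, although patients are randomised to three incentive structures

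*Protocol*

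**What the plan says.** The Primary Objective is "To test the efficacy of three financial incentive structures" on HbA1c. Under Patient Randomization, subjects are allocated in permuted blocks to a high, moderate or low frequency schedule, stratified by baseline HbA1c (8-10% or above 10%). The maximum reward is $300 in every arm, and the education component is described for all subjects.

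In the Analysis Plan for Primary Aim, "The primary framework for analysis is paired t-test", and "Change in HbA1c from baseline to 3-months (dependent variable) will be examined in each treatment arm", "using a type I error rate of 0.05". The Analysis Plan for Secondary Aims follows suit: "paired t-test will be used to evaluate change in BP, QOL, knowledge and self-care variables", again arm by arm. The exploratory analyses are descriptive within arms.

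Sample Size and Power is worded the same way. It claims "85% power to detect at least a 1.0 standardized effect size (difference in within group means in sd units") with 18 per arm, at "0.05, two-tailed test", and it applies the 85% to a 1.0-point HbA1c change within each arm. The number is then raised to 20 per arm for the intention-to-treat sample.

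On measurement, Data Collection Strategy describes blood for HbA1c at screening, where at least 8% is needed to proceed, and at follow-up: "All individuals randomized will have follow-up visits at 3 months, where survey questionnaires will be administered, and blood collected for HbA1c". Questionnaires, randomisation and blood pressure are listed for the baseline visit. No HbA1c draw is listed there.

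**The concern.** Randomisation supports a comparison of the arms, and no such comparison of outcomes is specified. A paired test asks only whether HbA1c moved within a group. With education and incentives in every arm, and no untreated arm, movement may come from the incentive, the education, usual care, a time trend or regression to the mean. The test therefore does not show that an incentive structure works, nor that one works better than another. Readers are likely to compare a significant arm with a non-significant one, which is not a comparison of arms.

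Selection makes regression to the mean a specific worry. Patients enter because one HbA1c value is at or above a cut-off. If change is measured from that same value, some fall is expected with no effect at all.

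**Working it through.** **Inputs from the protocol.** SD of HbA1c 1.5 points; correlation between repeated measures at most 0.5; two-sided 0.05; 18 per arm, 20 after inflation; target 1.0 point; entry at HbA1c of 8% or more.

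**Inputs assumed here.** Clinic HbA1c is normal with mean 7.5 to 9.0, and the correlation runs up to 0.8. None of these is in the protocol. Its SD of 1.5 describes trial measurements and is borrowed here for the clinic population.

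**1. The stated 85%.** A two-sample normal approximation with a 1.0 SD difference and 18 per arm gives 1.0/√(2/18) = 3.0, then Φ(3.0 − 1.96) = 0.851. So the figure reproduces from a between-arm formula at 1.0 SD, which is 1.5 points. It does not match the paired test described. At correlation 0.5 the SD of change is 1.5·√(2(1 − 0.5)) = 1.5. The paired t-test then has 97.9% power for 1.0 SD at n = 18, but for 1.0 point (1.0/1.5 = 0.667 SD) it has 76.0% at 18 and 80.7% at 20.

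**2. Disagreement when all arms are equal.** Suppose all arms truly fall by 1.0 point. The chance that the three tests do not all agree on significance is 1 − p³ − (1 − p)³.
- n = 20, p = 0.807: about 0.47
- n = 18, p = 0.760: about 0.55

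This step needs no assumption about regression to the mean.

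**3. Regression to the mean, if the screening value is the baseline.** With a = (8 − μ)/1.5 and λ = φ(a)/(1 − Φ(a)), the expected fall with no effect is (1 − ρ)·1.5·λ. The variance of change is (1 − ρ)²·1.5²·(1 − λ(λ − a)) + 1.5²·(1 − ρ²).

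| μ | ρ | λ | Expected fall | SD of change | P(one arm significant), n = 20 |
|---|---|---|---|---|---|
| 7.5 | 0.5 | 1.021 | 0.77 | 1.36 | 67% |
| 7.5 | 0.8 | 1.021 | 0.31 | 0.91 | 30% |
| 9.0 | 0.5 | 0.427 | 0.32 | 1.41 | 16% |
| 9.0 | 0.8 | 0.427 | 0.13 | 0.93 | 9% |

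The chance that at least one of three arms is significant, 1 − (1 − q)³, runs from about 25% to 96%. In a simulation of the first row with no effect, 96% of trials had a significant arm, while a between-arm F test on the same data rejected in 5.2%. Regression to the mean acts alike on randomised arms and drops out of their contrast.

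**4. What the arm comparison can deliver (SD 1.5, correlation 0.5).** The baseline-adjusted residual SD is 1.5·√(1 − 0.25) = 1.299. The 95% CI half-width for a pair at 20 per arm is 2.00 × 1.299 × √(2/20) = 0.82.

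| | 20 per arm | 18 per arm |
|---|---|---|
| Power for a 1.0-point pairwise difference | 66% | 61% |
| Difference detectable with 85% power | 1.26 | 1.34 |
| 95% CI half-width | 0.82 | 0.87 |

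The pairwise power ignores any preceding overall test. For assumed arm differences of 0, 0.5 and 1.0 points, the three-arm F test has about 55% power at 20 per arm. About 31 per arm would give 85% pairwise power for 1.0 point.

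**The case against.** The strongest reply is that this is a pilot, that the protocol frames each arm as its own within-group question, and that 60 patients are too few to compare arms. The low precision is real and should be stated. But the protocol calls its purpose a test of efficacy, and a pilot can report arm differences with confidence intervals. Whether three per-arm questions need family-wise control is arguable, and the point does not depend on it.

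A reader might infer more than the text supports in three ways.

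- **That the arms are compared in no way at all.** The protocol plans a check of the similarity of the arms, covariate-adjusted secondary analyses of unstated form, and analysis following CONSORT. None of these states an outcome contrast, and the supported claim is only that no between-arm test or estimate is specified.
- **That the screening value is the baseline.** No baseline-visit draw is listed and the strata start at the entry cut-off, which points that way. But the protocol never says so, and elsewhere it refers to outcomes measured at baseline. A separate baseline draw would reduce the regression effect.
- **That 0.13 to 0.77 points is the trial's bias.** The range rests on an assumed clinic mean and normality. Truncating an SD of 1.5 at 8% leaves an enrolled SD of 0.82 to 1.09 and an enrolled correlation of 0.30 to 0.70, which differ from the trial figures in Sample Size and Power. The range is illustrative.

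**Conclusion.** The point stands and needs correction before analysis. The protocol itself fixes within-arm tests for every primary and secondary outcome, so it is not a matter left to a later analysis plan. The central defect, that no specified analysis contrasts the randomised structures, rests on the text alone. The 47% disagreement rate (55% at 18 per arm) rests on the protocol's SD, its limiting correlation of 0.5 and a common 1.0-point fall. The false-significance range of about 9% to 67% per arm is conditional on the qualifying value being the baseline and on the assumed clinic distribution. Because usual care is named as comparator in the aims but not randomised, comparing the arms repairs the contrast between incentive structures and nothing beyond it.

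**What to change.** - **Primary analysis.** Fit one linear model of 3-month HbA1c on arm, baseline HbA1c and the randomisation stratum. Take the 2-df arm test first, then the three pairwise differences with 95% CIs. With exactly three arms, this order holds the family error at 5% without further adjustment.
- **Secondary outcomes.** Use the same model with each outcome's own baseline value.
- **Within-arm changes.** Report them with CIs as descriptive, without efficacy wording.
- **Baseline value.** State which HbA1c draw serves as baseline.
- **Sample Size and Power.** Replace the 85% within-arm statement with the between-arm figures in the second table above, or describe the pilot as an estimation study and give the expected CI half-width.
- **Scope.** State that the trial compares incentive structures with one another and cannot estimate an effect against usual care.

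The cost is protocol wording and modest analysis work. The model itself needs no new patients and no measurements beyond those planned. The price is a less favourable headline: about 66% power for 1.0 point at 20 per arm. Keeping 85% would mean about 31 per arm.

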### Analysis Plan for Secondary Aims:

1. To test the efficacy of three financial incentive structures in combination with technology intensified diabetes education and skills training intervention on blood pressure and quality of life in AAs with T2DM.

2. To test the efficacy of three financial incentive structures in combination with technology intensified diabetes education and skills training intervention on diabetes knowledge and self-care behaviors (medication adherence, diet, exercise).

Similar to the primary analysis, paired t-test will be used to evaluate change in BP, QOL, knowledge and self-care variables from baseline to 3-months (dependent variables) within each treatment arm (high, moderate and low frequency of financial incentives) using a type I error rate of 0.05.

**Analysis Plan for Exploratory Analyses.** Exploratory analyses to examine frequency of session attendance, frequency of uploads and average weekly glucose within the three different financial incentive structures. Univariate descriptive statistics and frequency distributions will be calculated, as appropriate for all variables along with two-sided 95% confidence intervals when appropriate.

## **HUMAN SUBJECTS RESEARCH**

### **PROTECTION OF HUMAN SUBJECTS**

#### **1. RISKS TO THE SUBJECTS**

##### **a. Human Subjects Involvement and Characteristics**

The overarching aim of this proposal is test the efficacy of three financial incentive structures in combination with technology intensified diabetes education and skills training intervention on blood pressure and quality of life in AAs with T2DM. 60 AAs with T2DM will be randomized to three groups with varying frequency of financial incentives: 1) High Frequency: financial incentives for weekly uploads plus average glucose, incentives for weekly attendance to educational sessions, and incentives at the end of the study for meeting HbA1c goals 2) Moderate Frequency: financial incentives for weekly uploads plus average glucose, and incentives at the end of the study for meeting HbA1c goals, and 3) Low Frequency: financial incentives at the end of the study for meeting HbA1c goals.

**Study clinics:** The study sites for this study are MUSC general medicine, endocrine, family medicine, and community primary care clinics.

**Patient eligibility criteria:** The study inclusion and exclusion criteria are as follows

**Inclusion Criteria:** 1) Age  $\geq 21$  years; 2) Clinical diagnosis of T2DM and HbA1c  $\geq 8\%$  at the screening visit; 3) Self-identified as AA; 4) Subject must be taking at least one oral medication or insulin for diabetes to assess medication adherence; 5) Subjects must be able to communicate in English; 6) Subjects must have access to a telephone (landline or cell phone) and/or Ethernet for the study period; and 7) Subjects must be willing to use the FORA monitoring system for 3 months.

**Exclusion Criteria:** 1) Mental confusion on interview suggesting significant dementia; 2) Participation in other diabetes clinical trials; 3) Alcohol or drug abuse/dependency; 4) Active psychosis or acute mental disorder; and 5) Life expectancy  $< 12$  months.

##### **b. Sources of Materials**

**1. Research Material & Data:** Sources of research material include medical history, research questionnaires, blood pressure readings, and blood specimens. The questionnaires will obtain information about demographics, clinical history, diabetes self-care, resource use, depression, and quality of life. Patients will provide ~10cc of blood for laboratory testing.

**2. Linkages to Subjects:** Subjects will provide identifying information in addition to research data. Paper documents pertaining to this study will be stored in locked file cabinets in both the clinical center and the data management center, and data will be entered into secure, password-protected web databases developed for this study. A database of name, contact address, telephone number, and other research identification numbers will be stored separate from the study database, for purposes of audit by the sponsor (NIH) and MUSC IRB, if necessary. Access to study data will be limited to research personnel.

**3. Collection of Data and Specimens:**

**Personnel:** Two half-time masters-level trained diabetes educators (DEs) will deliver the interventions; one full-time research assistant (RA) will conduct screening, consent, enrollment procedures, and questionnaire administration; a half-time data entry clerk (DC) will be responsible for data entry; and a part-time masters-level statistician will be responsible for data management (DM).

### **Potential Risks**

Potential risks to the patient include possible violation of the patient's privacy, discomfort with questions on the research questionnaire, discomfort and bleeding from blood draws, discomfort with BP measurement, and psychological distress. Details on how these risks will be minimized are discussed under adequacy of protection against risks below.

